## 2.4 Intervention.

All participants included in this study will receive usual care. Participants assigned to the mobile messaging-based intervention group will receive mobile text messaging that was regularly delivered by SMS (short messaging service) platform to remind, encourage and motivate patients to participate in the behaviors needed for improving glycaemic control and CVD risk factors management. About 500 text messages are included in this study, covering 7 aspects: general information about CVD and diabetes, healthy diet, physical activity, medical adherence, glucose monitoring, blood pressure control, smoking cessation. The content of text message is based on the recommendation from the Chinese Diabetes Society(23) and American Diabetes Association(24), a text mess bank in plain language was established and modified according to Chinese diet culture and language habits. 6 messages per week will be sent through the messaging platform during the 12-month study period. Researchers will save and check the delivery log to ensure successful delivery. At each visit, participants in the intervention group are asked to confirm or update the phone number and complete a dedicated satisfaction survey questionnaire to investigate the reading proportion and satisfaction with the text messages

| Category                                        | Content/Explanation                                                   | Example                                                                                                                                                                                                                                                                    |
|-------------------------------------------------|-----------------------------------------------------------------------|----------------------------------------------------------------------------------------------------------------------------------------------------------------------------------------------------------------------------------------------------------------------------|
| General education about CVD and diabetes | Basic information about CVD and diabetes                              | At present diabetes cannot be cured, but it can be controlled through a variety of treatment methods. It mainly includes five aspects: Diabetes self-management education and support, self-monitoring of blood glucose, healthy diet, physical activity and drug therapy. |
| Healthy diet                             | Encourage and guide patients to form a healthy diet and eating habits | Foods high in fiber or with a lower glycemic index or glycemic load, such as vegetables, fruits, soy products, whole grains, and dairy products without added sugar, is more recommended for people with diabetes.                                                         |
| Physical activity                        | Encourage and guide patients to exercise                              | Start exercising as a part of your daily life. Spend 20-30 minutes every day to do some exercise. We suggest you start with a brisk walk, which is simple but helpful!                                                                                                     |
| Medication adherence                     | Remind medication and popularize right knowledge about medication     | Regularly taking oral hypoglycemic drugs or injecting insulin is necessary for glucose control. Did you forget to take your medicine? Never mind, set a repetitive alarm on your phone to remind you.                                                                      |
| Glucose monitoring                       | Remind glucose monitoring and prevent hypoglycemia                    | Glucose monitoring is an important way to check your body, helping you assess whether you need to adjust your medication and lifestyle recently.                                                                                                                           |
| Blood pressure control                   | Remind blood pressure control and management                          | The main goal of antihypertensive treatment is to control blood pressure. The ultimate goal of antihypertensive therapy is to minimize the incidence and mortality of cardiocerebrovascular diseases in patients with hypertension.                                        |
| Smoking Cessation                        | Encourage and help smoking cessation                                  | Smoking is harmful! Nicotine can stimulate adrenaline secretion, directly causing high blood pressure and glucose fluctuations.                                                                                                                                            |

90 **2.5 Outcomes**

91 **2.5.1 Primary outcome**

92 The primary outcome comprised the mean changes in HbA1c levels, LDL-C levels, and SBP levels from  
93 baseline to 12 months simultaneously modeled for a single overall treatment effect.

94 **2.5.2 Secondary outcomes**

- 95 ● Change in HbA1c levels
- 96 ● Change in fasting blood glucose (FBG) levels
- 97 ● Change in lipid levels, included total cholesterol (TC) levels, triglycerides (TG) levels, high-density

- lipoprotein cholesterol (HDL-C) levels
- Change in blood pressure levels
- Change in body-mass index (BMI).
- Proportion of participants with controlled HbA1c, LDL-C, and BP levels at 12 months.
- Change in self-reported medication adherence measured by the Morisky medication adherence scale (MMAS).
- Change in health-related quality of life measured according to the 12-item Short-Form Health Survey Questionnaire.

## 2.6 Baseline and follow-up visits

### 2.6.1 Screening/baseline visit

The purpose of the screening / baseline visit is to confirm patients' eligibility and interest in the proposed study, and obtain informed consent, sociodemographic factors (age, sex, education, employment status), lifestyle habits (smoking status, drinking status, physical activity, diet), medications and medical history, physical measurements, and laboratory measurements. Body weight, height, waist circumference and blood pressure will be measured by trained staff using standard procedures. Fasting blood samples will be collected at baseline visit. Laboratory measurements include HbA1c, fasting blood glucose and lipids.

### 2.6.2. Follow-up and termination visits

Physical measurements data and laboratory measurements will be collected by the study staff every 3 month during the 12-month intervention. Information on lifestyle habits (smoking status, drinking status, physical activity, diet), medical record data and medications will be scheduled at 6, 12 months following the baseline visit. In addition, adverse events if happen will be confirmed by the researchers based on self-reported questionnaires and medical records.

Table 2 . Study visits and data collection

|                | S/R | M1 | M2 | M3 | M6 | M9 | M12 |
|----------------|-----|----|----|----|----|----|-----|
| Inform consent | X   |    |    |    |    |    |     |

|                                  |   |   |   |   |   |   |   |
|----------------------------------|---|---|---|---|---|---|---|
| Randomization                    | X |   |   |   |   |   |   |
| Demographic information          | X |   |   |   |   |   |   |
| Medical history and medications  | X |   |   |   | X |   | X |
| Lifestyle questionnaire          | X |   |   |   | X |   | X |
| Blood pressure                   | X | X | X | X | X | X | X |
| Body weight, waist circumference | X | X | X | X | X | X | X |
| HbA1c                            | X |   |   | X | X | X | X |
| Blood lipids                     | X |   |   | X | X | X | X |
| Blood glucose                    | X |   |   | X | X | X | X |
| Blood samples                    | X |   |   |   | X |   | X |
| Adverse event                    | X | X | X | X | X | X | X |

S/R: Screening and randomization

## 2.7 Measurements

### 2.7.1 Questionnaire

Information on age, sex, education level, smoking status, physical activity, diet, smoking status, drinking status, medical history (such as diabetes, hypertension, dyslipidemia, CVD), medication use, medication adherence and health-related quality of life will be collected from the standardized questionnaire. Medication adherence will be measured by the Morisky medication adherence scale (MMAS) (range, 0-8, with lower scores indicating lower adherence). 12-item Short-Form Health Survey Questionnaire will be used to obtain the health-related quality of life (25).

### 2.7.2 Physical measurements

The blood pressure of each participant will be measured three times at each visit by blinded research doctors or nurses using an automatic electronic sphygmomanometer (OMRON Company). During each visit, participants will be asked to rest for 5 minutes and take the measurement in a sitting position, and they should avoid alcohol, cigarettes, coffee or tea, and physical exercise for 30 minutes before blood pressure measurement.

Height, weight, and waist circumference will also be measured by the trained staff according to standard procedures.

### **2.7.3 Laboratory measurements**

Blood samples will be collected to measure the level of blood glucose, HbA1c and blood lipids after 10 hours of fasting. The plasma glucose concentration will be determined by hexokinase mediated reaction. HbA1c levels will be measured by High Performance Liquid Chromatography (HPLC). Automatic biochemical analyzer will be used to measure serum total cholesterol, LDL-C, HDL-C, and triglycerides. All measurements will be conducted at Guangzhou Kinmed Center for Clinical Laboratory.

## **3. Adverse events**

### **3.1 Definition of adverse events**

Adverse events (AE) are defined as the occurrence of new diagnosis or deterioration of diseases during the treatment. The causal relationship to the intervention will be further evaluated.

### **3.2 Definition of serious adverse events**

Severe adverse events (SAE) are defined as the occurrence of any acute life-threatening event, a hospitalization for any cause other than routine delivery, prolonged or permanent disability.

### **3.3 Surveillance and recording**

Protection of participants from risks related to the intervention is of paramount concern to the physicians. All participants will be evaluated for their medical history before enrollment. Contact information of the physicians is available for all the participants.

All participants should be contacted regularly to evaluate the occurrence, severity, and duration of physical discomfort during intervention. Evidence of the occurrence of adverse events should be based on participants' self-report rather than suggestive questioning. Any medical adverse events will be recorded and the nature, severity, and cause-effect relationship will be evaluated by physicians and recorded in a timely manner on case report forms.

### **3.4 Assessment of severity**

The severity of adverse events is assessed as follows:

Mild: usually temporary, and not affecting daily activities;

Moderate: causing discomfort and affecting normal activities, thought tolerable and not requiring participants to take any medication.

Severe: disrupting daily activities and intolerable, requiring participants to take medication immediately.

With regard to the causal-effect relationship, medical adverse events are divided into five categories: definite, probable, possible, unlikely, and unrelated. Only “definite” and “probable” are counted as adverse events.

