### **3.5 Treatment**

Any adverse events happen, appropriate care or medical treatment (if necessary) should be immediately provided to keep the safety of all participants. In addition, all adverse events and serious adverse events and treatment should be recorded and reported to the Principal Investigator and the Committee within 24 hours and complete the case report form.

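### Section 3.4 counts only events attributed to the text messages as adverse events, which contradicts Section 3.1 and leaves the counted AEs unable to show an excess of harm between arms

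*Protocol*

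**What the plan says.** Section 3.1 makes an adverse event depend on occurrence alone: "Adverse events (AE) are defined as the occurrence of new diagnosis or deterioration of diseases during the treatment". Cause comes afterwards, as a separate step: "The causal relationship to the intervention will be further evaluated".

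Section 3.4 sets up the causality scale, "medical adverse events are divided into five categories: definite, probable, possible, unlikely, and unrelated", and then turns it into a counting rule: "Only “definite” and “probable” are counted as adverse events".

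Section 3.2 is headed serious adverse events but words the term differently: "Severe adverse events (SAE) are defined as the occurrence of any acute life-threatening event". Its full list is "any acute life-threatening event, a hospitalization for any cause other than routine delivery, prolonged or permanent disability". It sets no relatedness condition and does not list death.

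On data capture, Section 3.3 says "Any medical adverse events will be recorded and the nature, severity, and cause-effect relationship will be evaluated by physicians", and Section 3.5 says "all adverse events and serious adverse events and treatment should be recorded and reported to the Principal Investigator and the Committee within 24 hours".

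Three other places matter. Section 2.4 describes messages for the intervention arm only; everyone receives usual care. Section 2.2 describes research nurses, investigators and statisticians as blinded. Section 2.3.3 makes severe adverse events one of the termination criteria.

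**The concern.** Randomisation is what lets a trial detect harm without anyone having to say what caused a given event: all events are counted in both arms and compared. A filter on attributed cause gives that up. Here the supposed cause is a text message that one arm never receives, so the filter works differently in the two arms even if the true event rates are the same.

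The harms most likely to matter are also the ones most likely to be filtered out. The messages encourage exercise and regular use of glucose-lowering drugs or insulin, and the message table in Section 2.4 itself mentions preventing hypoglycaemia. A hypoglycaemic episode after better insulin adherence would naturally be put down to the drug, not to the text that prompted it. An all-event comparison could reveal such an indirect effect; the Section 3.4 count would not.

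At stake is a report of few or no adverse events in 800 patients at raised cardiovascular risk, when that result comes largely from the counting rule.

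**Working it through.** The protocol gives no adverse event rate and no safety calculation, so there is no figure to reproduce. The check is mainly one of definitions, followed by an illustration of scale.

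**Definitions side by side**

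1. Under Section 3.1, a new diagnosis rated unrelated is an AE. Under Section 3.4, it is not counted as one. Both cannot govern the same tally.
2. Section 3.4 keeps two of five categories and drops three, including possible.
3. Causality is judged against the intervention (3.1), and only the intervention arm gets messages (2.4). A correctly judged control event is therefore never definite or probable, and the counted control number is 0.
4. If the judging physicians know the allocation, step 3 applies. If they are blinded, they cannot know whether a patient received any message, and a definite or probable rating has no sound basis. In neither case do the counted AEs compare the arms.
5. Section 3.2 includes hospitalisation for any cause. Section 3.4 speaks of adverse events and does not say whether it extends to SAEs. Read literally, the SAE tally is all-cause in both arms.
6. Death is not on the Section 3.2 list. Many deaths would follow a listed life-threatening event or hospitalisation, but a sudden death outside hospital might meet no listed criterion.

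**Illustration**

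Input from the protocol: 400 per arm (Section 5.1). Assumptions: the proportion p with an event is 5%, 10% or 20%; the share q of message-arm events rated definite or probable is 0-5%; there is one event per affected participant, and no dropout. Affected participants per arm = 400 × p. Counted in the message arm = 400 × p × q. Counted in control = 0.

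| p in both arms | Affected per arm | Counted, message arm (q = 0-5%) | Counted, control |
|---|---|---|---|
| 5% | 20 | 0-1 | 0 |
| 10% | 40 | 0-2 | 0 |
| 20% | 80 | 0-4 | 0 |

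With all events counted, 400 per arm, 80% power and two-sided 0.05, the detectable rises are:

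- from 5% to about 10.3%
- from 10% to about 16.8%
- from 20% to about 28.5%

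Take the middle case under the Section 3.4 rule. A true rate of 16.75% in the message arm is 400 × 0.1675 = 67 participants against 40 in control. At q = 5% the count is 67 × 0.05 = 3.4 against 0. Fisher's exact test gives p = 0.25 for 3 v 0 and p = 0.12 for 4 v 0. It gives 0.062 for 5 v 0 and first falls below 0.05 at 6 v 0 (0.031).

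The distortion can also run the other way. With identical 20% rates in both arms and q = 7.5%, the count is 80 × 0.075 = 6 against 0, a nominally significant difference with no excess at all. The counted difference depends on how readily events are attributed, not on how often they happen.

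**The case against.** The strongest reply is that nothing is lost: Sections 3.3 and 3.5 require events to be recorded with their causality and reported within 24 hours, so an all-cause table can be built at any time. Section 5.2.1 states no between-arm safety comparison, Section 4.3 uses adverse event reports for study management, and tabulation by arm is commonly left to a statistical analysis plan, which is not shown. Most of this stands and limits the consequence. It does not remove the defect. The counting rule is written in the protocol, and an analysis plan that counted every event would contradict it.

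The reply also blocks several stronger readings that a reader might infer:

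- *The whole safety comparison is empty.* Not supported. Section 3.2 keeps hospitalisation for any cause with no relatedness condition, and Section 3.5 names AEs and SAEs separately. The SAE tally survives unless the filter is extended to it.
- *The control count is zero whatever happens.* Too absolute. A blinded assessor could rate a control event probable. The zero holds for correctly judged events.
- *Hospitalisations would be lost.* They could drop out of the AE count, but as written they remain SAEs.
- *Deaths judged unrelated would never be counted.* Too strong. Leaving death off the list makes the definition incomplete, not empty.

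The mix of 'severe' and 'serious' is mainly wording. It carries some weight because Section 2.3.3 ties termination to severe adverse events, a phrase that could mean either the Section 3.2 list or the Section 3.4 intensity grade.

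**Conclusion.** The point holds for adverse events. Sections 3.1 and 3.4 contradict each other, and following Section 3.4 as written yields an AE tally that cannot show an excess of harm between arms: zero in control when events are correctly judged, and in the message arm only the few events firmly attributed to a text. Under the assumed rates, that is 0-4 counted in the message arm, where 20-80 participants per arm actually have an event. The conclusion follows from the definitions; the sizes rest on assumed event rates and attribution shares, because the protocol gives neither.

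For serious adverse events the claim is narrower. The protocol does not say whether the filter reaches them, and the definition omits death. The primary outcome, the sample size and the efficacy analysis are unaffected.

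**What to change.** - Section 3.4: delete the counting sentence. State that all recorded AEs and SAEs are counted by arm regardless of causality, with the five-level rating kept as a descriptor.
- State explicitly that no causality filter applies to SAEs.
- Section 3.2: add death to the SAE definition, and use 'serious' for the term being defined.
- Reconcile the use of 'severe' in Sections 2.3.3, 3.2 and 3.4, so that it is clear which meaning the termination criterion carries. Which meaning applies there is for the investigators to settle.

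The cost is wording and a slightly longer adverse event table. Section 3.3 already puts the events and their causality on the case report form, so nothing is added to the recording of AEs.

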### **4.3 Data reports**

Several standardized reports will be generated as follows: 1) participant recruitment and follow-up; 2)

demographics; 3) data quality and monitoring; 4) adverse events. These reports will be used for study management. These reports will be blinded to research personnel who collect study outcomes.

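### Section 3.4 counts only events rated definitely or probably related as adverse events, contradicting the cause-free definition in section 3.1, so the count does not measure adverse-event incidence by arm

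*Protocol*

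**What the plan says.** Section 3.1 of the Protocol sets the definition: "Adverse events (AE) are defined as the occurrence of new diagnosis or deterioration of diseases during the treatment". Causality comes second: "The causal relationship to the intervention will be further evaluated". Section 3.2 likewise puts no causal condition on SAEs; among them it lists "a hospitalization for any cause other than routine delivery".

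Section 3.3 covers recording: "Any medical adverse events will be recorded and the nature, severity, and cause-effect relationship will be evaluated by physicians". Section 3.5 covers reporting: "all adverse events and serious adverse events and treatment should be recorded and reported to the Principal Investigator and the Committee within 24 hours". Section 2.6.2 adds that "adverse events if happen will be confirmed by the researchers based on self-reported questionnaires and medical records", and Table 2 schedules AE collection at every visit.

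Section 3.4 grades severity, sets out five causality levels (definite, probable, possible, unlikely, unrelated), and closes with the counting rule: "Only “definite” and “probable” are counted as adverse events". AEs are one of the standardized reports in section 4.3, which describes them as "4) adverse events. These reports will be used for study management".

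Two design facts bear on this. Under section 2.4 both arms receive usual care and only the intervention arm receives messages. Under section 2.2 research nurses, investigators and statisticians are blinded to allocation.

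**The concern.** The same event can be an AE under section 3.1 and not one under section 3.4. Staff who rate an event as possibly related cannot tell from the Protocol whether it belongs in the AE report or must be reported within 24 hours.

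The rule also filters events by their relation to something only one arm receives. A safety summary from a randomized trial is useful because the same events are counted in the same way in both arms. A filter on relatedness to the messages cannot be applied on that footing. Anyone reading the resulting figure as the frequency of adverse events in each arm would be reading something else.

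**Working it through.** The Protocol gives no AE rate, AE count or AE hypothesis, so there is no figure to reproduce. The check sets the sections side by side.

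**Step 1: apply each section to the same event.**

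| Event | Causality rating | Section 3.1 | Section 3.2 | Section 3.4 |
|---|---|---|---|---|
| New diagnosis, no admission | definite or probable | AE | not an SAE on this ground | counted |
| New diagnosis, no admission | possible, unlikely or unrelated | AE | not an SAE on this ground | not counted |
| Hospital admission for a worsened disease | definite or probable | AE | SAE | counted |
| Hospital admission for a worsened disease | possible, unlikely or unrelated | AE | SAE | not counted as an AE; status as an SAE not stated |

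The second row is a direct contradiction: the event meets 3.1 in full and 3.4 removes it. Three of the five causality levels (5 − 2 = 3) are removed in this way. The fourth row is an ambiguity, because 3.4 does not say what happens to SAEs.

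**Step 2: look for text that reconciles the two.** Section 3.4 could be harmless if another section confined it to a table of related events, or restored a count regardless of cause. Nothing in the Protocol does either. Sections 3.3 and 3.5 speak of recording and reporting AEs, but they use the very term that 3.4 narrows, so they do not settle which events are meant.

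**Step 3: ask what the rating refers to.** The only causal reference is to the intervention (3.1), which is the messages. Usual care is common to both arms.

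**Step 4: follow the rule under each state of the rater's knowledge.**

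- *Rater blinded, as 2.2 states for investigators.* The physician judges whether messages caused the event without knowing whether any were sent. The filter need not favour either arm, but it has no factual basis, and the events that survive it are not AE incidence.
- *Rater knows the arm.* An event in a participant who was sent no messages can hardly be rated definitely or probably caused by them. The control count is then close to zero whatever the true rate. One possible route to this knowledge is the satisfaction survey that only intervention participants complete at each visit (2.4).

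In neither case does the counted figure measure AE incidence by arm.

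**The case against.** The strongest reply is that nothing is lost. Events in both arms are confirmed, recorded and rated on case report forms (2.6.2, 3.3), so a table regardless of cause can be built at any time. This stands, and it limits the harm to how events are counted and reported. It does not make the stated rule correct.

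Second, a reader might infer that 3.4 flatly contradicts 3.2 and discards unrelated SAEs. The text does not go that far. Section 3.4 never names SAEs, and 3.5 lists them as a separate item beside AEs. On that reading SAEs escape the filter. What remains is that the Protocol does not say which reading applies.

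Third, a reader might infer that the comparison between arms is certainly biased. That follows only if the rater knows the arm. Section 2.2 says investigators are blinded, and nothing says the physicians who rate causality see the satisfaction survey.

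Fourth, a reader might infer a loss of power to detect a safety difference. The Protocol supports no such figure. It plans no AE test, lists no AE outcome in 2.5, and gives no event rates. Even the direction is open: a filter that removed mainly background events could sharpen a real difference, while one that kept the same share of events in each arm would blur it.

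The point also cannot be set aside as detail for a statistical analysis plan. It is a counting rule that the Protocol itself states and that conflicts with its own definition.

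**Conclusion.** The point holds as a defect in the safety-counting rule. The contradiction between 3.4 and 3.1 is explicit and rests on no assumption. The unclear status of SAEs rated possible, unlikely or unrelated, under both 4.3 and 3.5, follows from the silence of 3.4. That the count does not measure AE incidence by arm follows from the messages going to one arm only, and it holds whether or not the rater is blinded; a bias in a known direction would need an unblinded rater.

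Its size cannot be expressed as a number of events, because the Protocol gives neither event rates nor the share expected in each causality level. The primary outcome and all secondary outcomes are untouched. The rule should be amended, but it does not threaten the trial's main conclusion.

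**What to change.** Replace the last sentence of section 3.4 with a rule that all recorded AEs and SAEs are counted and reported by arm regardless of causality. Keep the five-level rating as a descriptive field. If a count of definite and probable events is wanted, present it as a separate table labelled as related events. State in the same place that the causality rating does not decide whether an event enters the AE report in 4.3 or the 24-hour reporting in 3.5.

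The change is confined to section 3.4. It needs no new visits, since Table 2 already schedules AE collection throughout, and no new rating, since 3.3 already requires one. The cost is more events to tabulate and to report within 24 hours, many of them likely to be judged unrelated.
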